### Randomization

Randomizing individual providers is not ideal because of a high potential for contamination within facilities and goal of changing facility culture. A cluster RCT design allows us to address threats to internal validity and account for natural clustering of providers within facilities [57]. Forty facilities will be randomized to intervention (*N* = 20) and control (*N* = 20), with arms stratified by country(10 intervention and 10 control facilities in each country). To reduce the risk of contamination due to interaction of providers within the same sub-counties and districts, randomization will be at the sub-county/district level such that control and intervention facilities are not in the same sub-county/district. The facility randomization will be done by a statistician not directly involved in the study. The intervention group will receive all strategies of the *CPIPE* intervention strategies over a period of 6 months after the baseline data collection. At the end of the 6-month implementation, we will collect midline data. Facilities will then be encouraged to continue with the intervention activities without involvement of the study for an additional 6 months, with final data collection at 12 months (endline). The control group will not receive the CPIPE intervention during the 12-month data collection period but will maintain their usual facility level activities. We plan to implement the intervention in the control sites after the endline data collection (assuming preliminary effectiveness). The protocol complies with the standard protocol items for cluster randomized trials. The study design, outcomes, and participant flow are summarized in Figs. 2 and 3.

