#### Data collection

We will collect data at 3 time points in the intervention and control sites: baseline (T1) prior to the intervention start at each facility, midline 6 months post-baseline/intervention start (T2) to assess immediate impact, and endline 12 months after baseline (6 months post-intervention) (T3) to assess sustainability. Survey data will be collected utilizing Redcap programmed tablets. Process data will be collected throughout the study to assess intervention fidelity and implementation using study logs and Redcap. The provider cohort will be followed longitudinally for 12 months following baseline enrollment. The women’s sample will be multiple cross-sections, where data will be collected from 3 different groups of women at the 3 time points. We will use a mixed-methods approach. Quantitative data will be obtained from surveys followed by IDIs to qualitatively explore factors that may influence outcomes. We will also assess intervention fidelity through observations of intervention activities and a review of project logs [58, 59].

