### Analysis plan

#### Data quality assurance, initial analyses, and missing data

We will use Redcap to perform real-time checks for data quality assurance [69, 70]. We will use frequency tables and measures of central tendency and variability for continuous variables to characterize the sample overall and by randomization group. If the two groups differ significantly at baseline on one or more covariates, we will use methods based on the Rubin causal model (e.g., propensity scores, double-robust estimation) to obtain the desired effect estimates under the counterfactual assumption of balanced groups [71, 72]. We will address incomplete data with direct maximum likelihood (ML) and multiple imputation (MI) [73] because they make the relatively mild assumption that incomplete data arise from a conditionally missing-at-random (MAR) mechanism [74]. Auxiliary variables will be included to help meet the MAR assumption [75]. The proposed analyses will be conducted using STATA. All program code and results will be documented extensively and archived to enable future review, transparency, and results reproducibility.

##### Aim 1

We hypothesize that mothers in the *CPIPE* intervention group will have higher mean PCMC scores than mothers in the control group at 6 months (H1a) and 12 months (H1b) after baseline. To test hypotheses H1a-H1b, in primary analyses we will fit two-level linear mixed models (LMM) to the PCMC score. Each of these two models will include a fixed effect for the study arm with random intercepts for facility ID to account for the clustering of women within health facilities. Because we will compare *CPIPE* to control at 6 months and then repeat the same comparison at 12 months, alpha (α) will be set at 0.05/2 = 0.025 for each of these two planned comparisons. In secondary analyses for Aim 1, we will extend the LMMs for PCMC to include effects for age and SES and their interactions with the intervention group indicator to explore whether the *CPIPE* intervention differentially benefits younger and lower SES women. Sex as a Biological Variable is not applicable: all participants will be biological females.

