##### Aim 1 Power Analysis:

We used the NCSS PASS [76] module for a two-level multilevel model with a continuous outcome and randomization at the cluster (i.e., health facility) level to compute the minimum detectable effect size estimates for hypotheses H1a-H1b. We assumed power of 0.80, α = 0.025 per comparison, and *N* = 2000 women from 40 facilities. We further assumed ICC = 0.16 based on our previous data [20, 77]. The minimum detectable standardized mean difference was *d* = 0.41, which is between small and medium effect size, suggesting the proposed primary analyses have sufficient power to detect small to medium effects [78].

##### Aim 2

We anticipate that the intervention will positively impact the intermediate outcomes in our conceptual model (Fig. 1), leading to an improvement in PCMC. We thus hypothesize that, following *CPIPE* exposure, intervention providers will have, higher mean scores on provider knowledge (H2a); self-efficacy (H2b); enabling environment (H2c); behavior (H2d), and lower mean scores on work-related psychological effects (stress, burnout, and bias) (H2e) relative to control providers. To test these hypotheses, we will fit three-level LMMs to each intermediate outcome, with fixed effects for study arm, time, and their interaction, random intercepts for facility ID to account for clustering of providers within health facilities, and random intercepts, random slopes, and their covariance for person ID to account for clustering of repeated measurements within providers. We will perform time-averaged comparisons of repeatedly measured post-baseline observations of the key intermediate outcomes across study arms to examine *CPIPE* intervention effects.

In secondary exploratory analyses, we will investigate whether the intermediate outcomes measured for providers at 6 months mediate the relationship between *CPIPE* intervention assignment and PCMC at 12 months. These analyses will be conducted using principles of structural equation modeling (SEM) and causal mediation methods [1]. We will explore whether *sex as a biological variable* differentially affects intervention effects on the provider-level primary analyses by adding a sex main effect and a sex-by-*CPIPE* assignment interaction term to the LMM models. Sex as a biological variable is not applicable to the mediation analyses due to the outcome applying to women only.

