While facility data will be limited to *N* = 40 clinics, inferential analyses will be performed with *N* = 2000 women on distal outcomes. We focus on the key outcome of receipt of timely post-natal care. We hypothesize that among mothers giving birth in the study facilities, mothers who received care in the *CPIPE* intervention group will be more likely to receive postnatal care within 48 h than mothers in the control group at 6 months (H3a) and 12 months (H3b) after baseline. To test H3a and H3b, we will fit two-level generalized linear mixed models (GLMM) to the binary timely postnatal care variable collected at 6 months and at 12 months. Each model will include a fixed effect for study arm and random intercepts for facilities for clustering of women within health facilities. Because we will compare *CPIPE* to control at 6 months and at 12 months, α will be set at.05/2 = 0.025 for each comparison. We will use the same GLMM approach to test the effects of *CPIPE* on other distal outcomes. Additional secondary exploratory analyses for Aim 3 will explore whether the PCMC scores mediate the relationship between *CPIPE* intervention exposure and receipt of timely post-natal care. As in specific Aim 2, we will perform mediation analyses using SEM and causal mediation methods [79]. Sex as a Biological Variable is not applicable because all care recipients will be biological females.

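### Aim 1 primary tests: the fixed 0.025/0.025 split for 6 and 12 months is valid, but Holm's procedure dominates it at the same familywise error

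*Protocol article*

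**What the plan says.** Under Analysis plan, Aim 1, the hypotheses are that intervention mothers will have "higher mean PCMC scores than mothers in the control group at 6 months (H1a) and 12 months (H1b) after baseline". Each time point has its own two-level linear mixed model with a fixed effect for arm and a random intercept for facility. For multiplicity, "alpha (α) will be set at 0.05/2 = 0.025 for each of these two planned comparisons". The section gives no step-down, hierarchical or other sequential rule.

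The Aim 1 Power Analysis uses the same level: "We assumed power of 0.80, α = 0.025 per comparison, and *N* = 2000 women from 40 facilities". It adds "We further assumed ICC = 0.16 based on our previous data" and concludes "The minimum detectable standardized mean difference was *d* = 0.41".

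Three other statements bear on the point:
- Randomization: "Forty facilities will be randomized to intervention (*N* = 20) and control (*N* = 20", so allocation is 1:1.
- Data collection: "data will be collected from 3 different groups of women at the 3 time points". The two post-baseline comparisons therefore use different women in the same facilities.
- Safety monitoring: no interim analysis is planned to decide on stopping the study.

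**The concern.** With a fixed split, the outcome of one comparison never helps the other. Suppose the 6-month p-value is 0.001 and the 12-month p-value is 0.03. Under the current rule the 12-month result is not significant, although the 0.05 familywise budget would support claiming it.

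This pattern is plausible here. The midline survey measures immediate impact. For the following six months facilities are encouraged to continue without study involvement, and the endline survey then measures whether the effect lasts. A clear early effect followed by a weaker late one is where the fixed split costs most. What is at stake is power for the second of the two primary claims, not the validity of either.

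**Working it through.** **Inputs from the article:** 2000 women per time point, 40 facilities (20 per arm), hence 2000/40 = 50 women per facility on average; ICC 0.16; power 0.80; alpha 0.025 per comparison.

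**Assumed, because the article does not give it:** the correlation between the 6- and 12-month test statistics.

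**1. Reproduce the stated detectable difference.**
- Design effect = 1 + (50 − 1) × 0.16 = 8.84.
- Standard error of d = √(4 × 8.84/2000) = 0.133.
- d = (z₀.₉₈₇₅ + z₀.₈₀) × SE = (2.241 + 0.842) × 0.133 = 0.410.

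This matches the stated 0.41 and shows that 0.025 was taken as two-sided; a one-sided 0.025 would give 0.373. A t reference with 38 degrees of freedom would give 0.424.

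**2. Power at the second step.** Once one hypothesis is rejected, the other is tested at two-sided 0.05. At d = 0.41, power is then 86.9% instead of 80.0%. The difference detectable with 80% power falls to (1.960 + 0.842) × 0.133 = 0.373.

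**3. Familywise error of Holm.**
- Both nulls true: an error requires the smaller p-value to be at most 0.025, which has probability at most 2 × 0.025 = 0.05.
- One null true: an error requires that null's own p-value to be at most 0.05, which has probability at most 0.05.

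Neither step uses the correlation. Simulation agrees. Under the global null the familywise error is the same for both rules, 0.0495 at correlation 0 and 0.036 at 0.905. With one true effect of 0.41, Holm's false rejection rate for the other hypothesis is 0.037 to 0.045.

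**4. Range of correlations.** Let CAC be the cluster autocorrelation, that is, the correlation of facility effects between the two surveys. The correlation of the tests is then ICC × CAC / (ICC + (1 − ICC)/50) = 0.16 × CAC / 0.1768 = 0.905 × CAC. CAC values of 0, 0.5, 0.8 and 1 give 0, 0.452, 0.724 and 0.905.

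**5. Power, true d = 0.41 at both times** (one million simulated pairs per row):

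| Correlation | Per test, fixed split | Per test, Holm | Both, fixed split | Both, Holm | At least one, either rule |
|---|---|---|---|---|---|
| 0 | 80% | 85.6% | 64.1% | 75.2% | 96.1% |
| 0.452 | 80% | 84.7% | 68.2% | 77.5% | 91.9% |
| 0.724 | 80% | 84.0% | 71.7% | 79.6% | 88.4% |
| 0.905 | 80% | 83.2% | 75.2% | 81.6% | 84.9% |

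Hand check at correlation 0: per test, 0.800 + (0.869 − 0.800) × 0.800 = 0.855; both, 0.800² + 2 × 0.069 × 0.800 = 0.750. These agree with the first row to rounding.

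**6. Unequal effects.** With d = 0.41 at one time and 0.205 at the other, power for the weaker effect rises from 24.2% to 32.0-33.8% over the same correlations.

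In no simulated pair did the fixed split reject a hypothesis that Holm did not.

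**The case against.** The strongest reply is that nothing here is wrong. The split is pre-specified, controls familywise error, and is carried into a power calculation that reproduces. The trial is therefore sized for 80% per comparison with the correction already paid for, and choosing between two valid procedures can look like taste. The first part stands. The second does not quite: Holm rejects everything that the fixed split rejects, at the same familywise level, so on the test decisions there is no trade-off.

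The fixed split does buy two things. Each time point has its own threshold that can be applied on its own, and simple 97.5% simultaneous intervals always match the decisions. Under Holm, a 6-month p-value between 0.025 and 0.05 must wait for the 12-month result. If the second step rejects with a p-value in that range, the 97.5% interval includes zero although significance is declared. Both costs are real but small. With no stopping decision planned at 6 months, both p-values can be ordered after endline.

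A reader might infer three stronger points that the article does not support:
- **That the split is a mistake or leaves the trial underpowered.** It is valid, no stated figure changes, and the probability of at least one significant primary comparison is identical under both rules.
- **That sharing the same 40 facilities strengthens the case.** Holm does not use the correlation, and its advantage shrinks as correlation rises: from about 5.5 to about 3 points per test, and from about 11 to about 6 points for both.
- **That Aim 3 needs the same change.** H3a and H3b use the same 0.025 level, but the article calls that aim exploratory. It sets the level "for each comparison. We will use the same GLMM approach to test the effects of" the intervention on other distal outcomes, with no overall error claim. Refining two tests there has little confirmatory meaning.

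**Conclusion.** The point holds as a low-priority improvement to the Aim 1 primary analysis. At the design effect size at both times, Holm adds about 3 to 5.5 percentage points of power per comparison and about 6 to 11 points for establishing both.

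The direction of the gain and the error control need no assumption about dependence. The size rests on the article's ICC, equal facility sizes of 50, a normal approximation with two-sided tests, and the assumed correlation range of 0 to 0.905. In practice the rules differ only when one p-value is at most 0.025 and the other lies between 0.025 and 0.05. Estimates are the same either way, and the current rule introduces no bias or excess error.

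**What to change.** Replace the multiplicity sentence under Aim 1 with: *H1a and H1b will be tested after endline with the Holm procedure at familywise alpha 0.05: the smaller p-value against 0.025 and, if rejected, the other against 0.05.*

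Leave the Aim 1 power statement as it is; d = 0.41 at 0.025 remains a conservative figure. Add a line saying that 97.5% intervals will be reported and that such an interval may include zero when the second step rejects. Aim 3 can stay unchanged.

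The cost is one or two sentences, with no change to sample size or data collection. The change should be made before any outcome comparison by arm is seen, since a later switch would look data-driven.

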#### Assess the effectiveness of the CPIPE intervention on PCMC

We hypothesize that *CPIPE* will improve PCMC for all women, but especially for low SES women. In addition, we will conduct a cost-effectiveness analysis of CPIPE on PCMC.

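### As written, the exploratory SES-by-arm and age-by-arm models name only a facility random intercept, so their standard errors are too small if the SES or age slope varies across facilities

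*Protocol article*

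**What the plan says.** The Aim 1 part of the Analysis plan defines the two primary models (6 and 12 months) as follows: "Each of these two models will include a fixed effect for the study arm with random intercepts for facility ID". For the secondary analyses it extends these models "to include effects for age and SES and their interactions with the intervention group indicator", with the purpose "to explore whether the *CPIPE* intervention differentially benefits younger and lower SES women". The extension lists fixed terms only. The random part of the extended model is not restated.

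The Aims section words the equity expectation more strongly. There, CPIPE "will improve PCMC for all women, but especially for low SES women", as part of the Aim 1 hypothesis.

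The only significance level given for Aim 1 belongs to the two main comparisons: alpha "will be set at 0.05/2 = 0.025 for each of these two planned comparisons". None is assigned to the interactions. For Aim 2 the article does name random slopes and their covariance with the intercept, but at provider (person) level.

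**The concern.** An interaction between a cluster-level treatment and a woman-level characteristic compares facility-specific slopes. Here it is the average SES (or age) slope in 20 intervention facilities against the average in 20 control facilities. A random intercept lets facilities differ in their mean PCMC score, but it forces all facilities within an arm to share one slope. If the true slopes differ, that variation is missing from the interaction's standard error, and the test rejects too often.

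Slope variation is plausible in this trial. The facilities span two countries and four counties or regions, and the intervention acts on provider bias and facility culture, which could make SES gradients differ by facility. At stake is the equity statement. Facility-to-facility differences in the SES gradient could be read as evidence that CPIPE benefits low-SES women more.

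**Working it through.** **Inputs from the protocol article.** 2000 women per time point in 40 facilities (50 per facility on average), 20 facilities per arm, ICC 0.16, power 0.80, alpha 0.025 per main comparison.

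**Reproducing the plan's own figure.** Design effect = 1 + (50 − 1) × 0.16 = 8.84. With two-sided alpha 0.025, d = (2.241 + 0.842) × √(4 × 8.84 / 2000) = 0.410. This matches the stated 0.41. The article gives no corresponding figure for the interactions.

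**Interaction: assumptions.** Total outcome SD 1, so the residual within-facility variance is 1 − 0.16 = 0.84. Facilities are of equal size. The covariate is standardised, with share v of its variance within facilities. The slope SD across facilities, τ, is in outcome SD per covariate SD. τ and v are not in the document. The 5% two-sided level is also an assumption, since no alpha is set for these tests.

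**Formula.** The sampling variance of one facility's slope is about 0.84 / (50v). The true variance adds τ². The ratio of true to reported variance is therefore

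R = 1 + 50·v·τ² / 0.84,

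and the true size of a nominal 5% test is 2 × [1 − Φ(1.96 / √R)].

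**Results with v = 1.**

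| Slope SD τ | R | True SE / reported SE | True size |
|---|---|---|---|
| 0 | 1.00 | 1.00 | 5.0% |
| 0.03 | 1.05 | 1.03 | 5.6% |
| 0.05 | 1.15 | 1.07 | 6.7% |
| 0.07 | 1.29 | 1.14 | 8.5% |
| 0.10 | 1.60 | 1.26 | 12.1% |
| 0.14 | 2.17 | 1.47 | 18.3% |

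**Covariate partly between facilities.** With v = 0.7 and τ = 0.10, R = 1 + 35 × 0.01 / 0.84 = 1.42, and the size is about 10%.

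**Simulation, standardised covariate** (40 × 50, 2000 runs). At slope variances 0.005, 0.01 and 0.02 (τ about 0.07, 0.10 and 0.14), the random-intercept model rejected in 8.2%, 11.3% and 18.0% of runs. A t-test on facility-specific slopes rejected in 4.0%, 3.9% and 4.7%.

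**Second check, binary modifier split 50/50 in every facility** (REML fits, 1000 runs per value). At slope SD 0, 0.1, 0.2 and 0.3, the formula gives 5.0%, 6.7%, 11.9% and 19.4%. Simulation gave 3.6%, 5.7%, 11.6% and 17.8%. Adding a facility random slope at 0.2 gave 4.7% (300 runs). A 50/50 binary variable has SD 0.5, so 0.2 on this scale equals 0.10 per covariate SD, and the two calculations agree at about 12%. With a 20% share in the low-SES group the inflation is smaller: 6.1%, 9.4% and 14.7% at 0.1, 0.2 and 0.3.

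**The case against.** The strongest reply is that the article never says the interaction models have a random intercept only. It gives the random part for the primary models and then lists added fixed terms. Its Aim 2 secondary analysis by sex is abbreviated in the same way. The full random structure of a secondary model is often left to the analysis plan, which is not shown. This stands in part: a reader might infer that random slopes are excluded, and the text does not go that far. But intercept-only remains the natural reading. The stated base model has one random effect, the extension adds none, and the article names random slopes where it wants them.

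Second, the harm depends wholly on a slope variance that nobody has stated. With none, the model is correct, and at τ = 0.03 to 0.05 the excess is slight. Quoting only 8–18% would leave out this low end, and taking all covariate variance as within-facility pushes the figures up. Both points stand, so the range should start at 5%.

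Third, the analysis is labelled secondary and exploratory and carries no alpha. This also stands, although the Aims section words the SES effect as a hypothesis.

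Finally, random slopes are not the only remedy. SES coding is not visible, and a categorical SES would need several slope variances from 40 facilities. Cluster-robust variance would also work. This bears on the form of the fix, not on the need for one.

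**Conclusion.** The point holds as a conditional one. The interaction models, as described, understate the standard error if the modifier's slope varies across facilities. Under the assumptions above, a nominal 5% test has a true size from 5% (no slope variation) to about 18% (τ = 0.14). It is 11–12% at τ = 0.10, or about 10% there if 70% of the covariate variance is within facilities. Where in this range the trial will fall cannot be told from the document.

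A reader might infer that the trial's main conclusion is at risk. It is not: the H1a and H1b tests do not involve these slopes, and d = 0.41 reproduces. Nor does the text support saying that a false equity claim is likely. The analysis is exploratory, and the inflation may be negligible. The point is worth settling because the Aims section makes the larger benefit for low-SES women part of the hypothesis, and the remedy needs no new data.

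**What to change.** In the SES-by-arm and age-by-arm models, add a facility-level random slope for the modifier being tested, and test the interaction with small-sample degrees of freedom. State in advance that, if the slope model does not converge, facility-cluster-robust variance with a small-sample correction will be used instead. If the analysis plan already contains this, the article's description only needs to be aligned with it.

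The cost is a line or two of specification, somewhat wider intervals and a possible convergence fallback. If the slope variance is estimated as zero, the fit reduces to the model now described. If it is not zero, the wider interval is the honest one. For the 50/50 binary modifier with slope SD 0.2, the interaction detectable with 80% power at two-sided 5% is 0.29 SD, not the 0.23 SD that the intercept-only standard error implies.
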